### Interventions

#### Omega-3 and placebo

The ω3 capsules were donated by Naturalis®, Nutrition and Pharma Company, São Paulo, Brazil. Each capsule contains 1 g of fish oil in the form of triglycerides, which is equivalent to about ≈ 750 mg of ω3 ([EPA–190 mg; DHA–550 mg], Table 1). The quality of the oil was certified by mass spectrometry (as shown by the Omega-3 determination method below). The heavy metals are under a minimum limit allowed daily intake (arsenic [<0.1 ppm], cadmium [<0.01 ppm], lead [<0.05 ppm], and mercury [<0.005 ppm]). Placebo pills consist of 1 g of mineral oil and were donated by the Catalent Pharma, Inc., Company, Sorocaba, Brazil.

**Table 1 Tab1:** Fatty acid composition of a capsule containing 1 g of pure fish oil

Carbons/insaturations/ω-position	Nomenclature (IUPAC)	mg/g
**C8:0**	Octanoic acid, methyl ester	0.0411
**C10:0**	Decanoic acid, methyl ester	0.0564
**C14:0**	Methyl tetradecanoate	0.3816
**C16:0**	Hexadecanoic acid	1.4015
**C16:1**	Hexadecenoic acid	0.6626
**C18:0**	Methyl stearate	1.8020
**C18:1 (ω9)**	Octadecenoic acid	3.6400
**C18:2 (ω6)**	Octadecadienoic acid	0.3841
**C18:3 (ω3)**	Octadecatrienoic acid	0.1981
**C19:0**	Nonadecanoic acid	0.1619
**C20:1**	cis-11-Eicosenoic acid	3.5847
**C20:1**	cis-13-Eicosenoic acid	0.5901
**C20:2 (ω3)**	8,11-Eicosadienoic acid	0.4160
**C20:2 (ω6)**	11,14-Eicosadienoic acid	0.4051
**C20:3**	Eicosatrienoic acid	0.2284
**C20:4 (ω6)**	Eicosatetraenoic acid	1.6491
**C21:0**	Heneicosanoic acid	0.3023
**C20:5 (ω3)**	Eicosatetraenoic acid	19.0560
**C22:0**	Docosanoic acid	0.8260
**C22:1**	Docosenoic acid	6.3434
**C22:4 (ω6)**	Docosatetraenoic acid	0.3351
**C22:6 (ω3)**	Docosatetraenoic acid	55.0547
**C24:0**	Tetracosenoic acid	2.4781
	∑SAT	7.45
	∑MONO	14.8208
	∑POLY	77.7266
	∑**ω6**	2.7734
	∑**ω**3∗	74.3087

*IUPAC* International Union of Pure and Applied Chemistry, *ω* Omega, *Σ* sum, *SAT* saturated fatty acids, *MONO* monounsaturated fatty acids, *POLY* polyunsaturated fatty acids. *EPA, DHA plus other ω3 species

#### Procedures

Figure 1A illustrates the simplified acute and chronic intervention design, and Fig. 1B illustrates the overall design and subject flow through the study. Participants may be withdrawn from the study at their request. Upon the first meeting, after being fully informed about the study and all risk factors, patients will be asked to sign the informed consent form. At this moment, the clinical questionnaire will be administrated. Instructions on a blood collection and body bioelectrical impedance test will be given. A second meeting will follow to conduct the randomization of the groups. Body composition and anthropometric profiles will be assessed, and the blood will be collected from all participants. Participants will be instructed to fill three dietary records. After randomization and 12 h of fasting, in the third meeting, the acute supplementation phase will begin. Initially, participants will perform the bioelectrical impedance test before the blood collection and before the ingestion of three capsules of placebo or three capsules of ω3 (totaling 2.2 g of ω3 [EPA–570 mg, DHA–1650 mg]), depending on the group in which they were randomized. In the meantime, because they have to wait for 3 h for the second blood collection to assess the ω3 bioavailability and ability to activate the GPR120 receptor, a 24-h recall (R24h), three dietary records will be administered and physical activity level, and anthropometric profiles will be evaluated. At the end of this meeting, an amber plastic flask protecting the capsules from light and oxygen will be provided to each participant, containing capsules available for 28 days of supplementation (3 caps/day or 2.2 g of ω3). Two days after this last meeting, the patients will report by phone call their R24h. At the last meeting and after 12 h fasting, all these assessments will be repeated.

**Fig. 1 Fig1:**
[figure not shown]
Experimental interventions scheme and detailed subject flow. **A** After the screening and randomization period, the selected participants will be fasting for 12 h. At the hospital service, body composition will be carried out, followed by the blood collection for biochemical and mass spectrometry analysis. Immediately, participants will take their placebo or ω3 capsules and wait for 3 h. Anthropometric measurements will then be performed, the same collections will be repeated, and another part of the blood will be separated to an immunoprecipitation test to verify the association between GPR120 and βarr2 proteins. After 30 days of supplementation, all measurements will be repeated with the inclusion of immunoblot blood tests and polymorphic GPR120 gene analysis. **B** Detailed flow through the study. ω3 Omega-3. IPAQ International Physical Activity Questionnaire

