## Subjects and methods

### Study design and settings

This is a triple-blinded (investigators, statistical analysts, and participants), single-centered, randomized placebo-controlled, prospective intervention trial. This protocol is written following the Standard Protocol Items: Recommendations for Interventional Trials (SPIRIT) checklist [37]. The study is designed to investigate the molecular action mechanisms of ω3 as antiinflammatory and anti-ER stress through GPR120 receptor in peripheral blood mononuclear cells (PBMC) and leukocytes of overweight and obese subjects with visceral obesity and non-alcoholic fatty liver disease (NAFLD). The study protocol was approved by the Ethics Committee of the Federal University of Sergipe (#80476517.2.0000.5546) and registered at the Brazilian Registry of Clinical Trials (#RBR-7x8tbx), on May 10, 2018, retrospectively registered: https://ensaiosclinicos.gov.br/rg/RBR-7x8tbx. All outpatients will be informed by study design before signing the informed consent form.

In the first part of the intervention (acute measurement [3 h after the first capsule intake]), the surrogate outcomes will be [1] ω3 fatty acid concentration in bloodstream, [2] association between GPR120 and βarr2 proteins, and [3] ω3 fatty acid concentration into PBMCs. In the second part, after chronic treatment (28 days of supplementation), the primary outcome will be considered the reduction (upper to 10%) in the TNFα and IL6 protein contents in PBMCs. Both parts of the intervention will be carried out in PBMC and leukocytes. Outcomes such as body weight, waist circumference, and glycemia will not be considered due to short supplementation time and study aim.

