#### Data treatment and statistical aspects

A steering committee will be organized for trial supervision. The process of data collection and management will be monitored by them. The committee may recommend and request the principal investigator to make some changes to the plan. To increase the security and data quality, the records will be inputted at the bank by one person and checked by another one. Data analysis will be performed according to the intention-to-treat principles [56]. The software Statistical Package for Social Sciences (SPSS), v. 22.0, will be used for data entry and analysis. Statistical analysis will be performed through descriptive analysis, with numerical variables expressed as the mean and standard deviation (SD) or median and interquartile range. All data will be subjected to the Shapiro-Wilk normality test. First, a two-way analysis of variance will be performed to check intra- and intergroup differences. Time will be added as a repeated factor, treatment as an independent factor, and the other variables (e.g., anthropometric data, food intake, blood analysis) as covariates.

The paired Student’s *t* test or Wilcoxon’s test will be used to compare the time effects. The Student’s *t* test and Mann-Whitney *U* test will be used to investigate group differences (placebo and treatment). All tests will be considered significative *P*<0.05. After trial completion, the principal investigator (PI) will be responsible for data archiving and preservation. Only investigators can access data. The PI will be responsible to terminate the trial at any moment.

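### The Figure 1 legend brings in the primary-outcome assay only at the final visit, which contradicts a primary outcome and analysis that need a pre-dose value

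*Protocol article*

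**What the plan says.** The Study design section of the protocol article defines the chronic-phase endpoint: "the primary outcome will be considered the reduction (upper to 10%) in the TNFα and IL6 protein contents in PBMCs". The section on immunoblotting and immunoprecipitation lists TNFα and IL6 among the proteins measured by immunoblot. The statistical section states "Time will be added as a repeated factor" and adds paired t or Wilcoxon tests for time effects, and t or Mann-Whitney tests between groups.

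The Figure 1 legend goes through the blood draws in order:

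- **Before the first capsules:** body composition, "followed by the blood collection for biochemical and mass spectrometry analysis".
- **Three hours later:** the same collections again, and "another part of the blood will be separated to an immunoprecipitation test to verify the association between GPR120 and βarr2 proteins".
- **End of supplementation:** "After 30 days of supplementation, all measurements will be repeated with the inclusion of immunoblot blood tests and polymorphic GPR120 gene analysis".

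The Procedures text says of the final visit only that "At the last meeting and after 12 h fasting, all these assessments will be repeated", and it names no immunoblot at any visit. (The legend's 30 days, where the text has 28, is a separate discrepancy.)

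**The concern.** The legend's wording is cumulative: each draw adds something to the one before. Immunoprecipitation is added at 3 h. Immunoblotting and GPR120 genotyping are added at the final visit. Read that way, TNFα and IL6 protein would be measured once per participant, after treatment. A reduction within a person, a repeated time factor and a paired test each need at least two values.

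The error could not be repaired later. The laboratory section has cells homogenized immediately after isolation, so a pre-dose lysate that is not prepared on the day is lost. The GPR120-βarr2 association, an acute surrogate outcome, would also lack a pre-dose value. Genotyping at the final visit would miss anyone who had left by then.

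**Working it through.** **1. Which text dates the immunoblot?**

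| Place in the protocol article | What it says about timing |
|---|---|
| Abstract | Attaches pre/post timing to anthropometry, intake, activity, lipids, fatty acids and glycemia; the next sentence, on PBMC proteins, gives no time point |
| Assessments to randomization | Blood list contains no PBMC protein |
| Procedures | Blood is drawn before and 3 h after the first capsules; no immunoblot named |
| PBMC isolation; Immunoblotting | No visit given |
| Fig. 1 legend | Immunoblot introduced at the final visit |
| Table 2 (detailed schedule) | Not visible |

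The legend is the only visible text that dates the assay, and it gives the final visit.

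**2. What can be computed if the legend is followed?** With one post-treatment value per person, the time factor, the paired tests and a within-person percentage reduction are not available. The between-group t or Mann-Whitney test on final values is.

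**3. Does the sample size depend on a baseline?** Inputs from the Sample size section: two groups, d = 1.15, α = 0.05 (taken as two-sided), power 85%.

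- Normal approximation: 14 per group.
- Noncentral t: 14.6, so 15.
- Mann-Whitney, relative efficiency 0.955: 14.6/0.955 = 15.3, so 16, which matches the stated 16.

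This is a two-independent-group calculation with no pre-post correlation, so the stated n does not presuppose a baseline.

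**4. What would a pre-dose value add?** The protocol gives no correlation ρ between pre-dose and final values, so ρ = 0.3, 0.5 and 0.7 are assumptions. Effective standardized differences:

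- final value only: d = 1.15
- final value adjusted for the pre-dose value (ANCOVA): 1.15/√(1−ρ²) = 1.21, 1.33, 1.61
- unadjusted change score: 1.15/√(2(1−ρ)) = 0.97, 1.15, 1.48

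With two time points, the treatment-by-time test in a repeated-measures ANOVA without baseline adjustment is the change-score test. Power by noncentral t, two-sided 5%, at the planned 16 evaluable and at 13 (22 × 0.6 = 13.2, the protocol's own dropout figure applied to 22):

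| | 13 per arm | 16 per arm |
|---|---|---|
| Final value only | 0.803 | 0.882 |
| ANCOVA, ρ = 0.3 / 0.5 / 0.7 | 0.839 / 0.901 / 0.976 | 0.910 / 0.953 / 0.993 |
| Change score, ρ = 0.3 / 0.5 / 0.7 | 0.662 / 0.803 / 0.953 | 0.758 / 0.882 / 0.982 |

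A pre-dose value raises power throughout this range if it is used for adjustment. As an unadjusted change score it costs power at ρ = 0.3 and is neutral at 0.5.

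**5. Genotype.** 0.4 × 44 = 17.6, so about 18 of 44 genotypes would be missing if the whole dropout allowance occurred before the final visit and no earlier blood were used. This is an upper figure.

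**The case against.** A reader might infer that the trial has no baseline for its primary outcome. The documents do not establish that. Table 2, cited as the detailed schedule, is not visible. Procedures calls Figure 1A simplified. The legend never says that immunoblotting is done only at the end. The planned repeated factor and paired tests suggest that the authors intend a pre-treatment measurement, and the isolation section sends PBMCs to immunoblotting without limiting this to a visit. A loosely worded legend is quite possible. This stands, and it limits the point to a contradiction that must be resolved.

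A reader might also infer that immunoprecipitation happens only at 3 h. It does not: the legend repeats all measurements at the end, and what is missing is a pre-dose value. That assay serves the GPR120-βarr2 outcome and has no bearing on a TNFα or IL6 baseline.

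Nor would the trial be invalid with final values alone. Randomization keeps the between-arm comparison unbiased, the sample size was computed for such a comparison, and the acute association has a concurrent placebo arm. The genotype argument is modest, because the Discussion concedes that the sample is small for studying the variant.

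None of this removes the conflict. The article gives a time for the assay, and that time does not fit the endpoint or the analysis.

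**Conclusion.** The point holds as an inconsistency. The legend introduces the primary-outcome assay and the genotyping at the final visit and shows no pre-dose immunoprecipitation, while the endpoint and the planned time-based tests need a pre-dose value. Followed literally, it removes the time factor, the paired tests and any within-person reduction for the primary outcome, and leaves a valid but less informative comparison of final values.

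The loss of the planned analyses follows from the text alone. The power figures rest on assumed correlations, on d = 1.15 and on 13 or 16 evaluable per arm, and are illustrative. They also show that the gain depends on baseline adjustment. The main caveat is the unseen Table 2: if it lists a pre-dose immunoblot, only the legend needs correcting. The change should be made, because a missed pre-dose lysate cannot be recovered.

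**What to change.** - Correct the Figure 1 legend. State there and in the immunoblotting section that PBMC lysate from the existing pre-dose draw at the third meeting is kept and immunoblotted for TNFα, IL6 and β-actin, and immunoprecipitated for GPR120-βarr2, as at the final visit. Check that Table 2 agrees.
- Define the primary effect as the between-arm difference in the final value adjusted for the pre-dose value, in place of an unadjusted change score.
- Genotype all randomized participants from the pre-dose sample, so that dropouts are not lost.

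The blood is already drawn before dosing, so the cost is splitting that sample, extra gel lanes and reagents, and some rewording. How samples are arranged on membranes is a laboratory choice outside this fix.

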#### Blinding

The practitioners, participants, outcome assessors, and statisticians will be kept blinded to treatment allocation throughout the trial. No toxic/adverse effects, beyond eructation, have been reported in previous studies using Omega-3 in a similar dose adopted by this study. Capsules will be prepackaged into opaque and identical containers labeled with codes by a local pharmacy, with the investigator’s details and supplementation instructions. This ensures the total blinding of both the participants and investigators. In the event of adverse events, clinicians will be able to unblind participants if they consider this necessary.

#### Safety, compliance monitoring, and participant retention

During follow-up, once a week, participants will report adverse events by phone, which is expected such as eructation, followed by uncomfortable gastric odor. The weekly contact will also promote participant retention to complete the study. In the case of significant adverse effects, the participant will be evaluated by the medical service from the hospital. Together with medical service, the nutritionist leader of this project will be responsible for participant stopping. Treatment compliance will be assessed by the plasma fatty acid content of patients at the beginning and the end of the experiment, which will be analyzed using a gas-chromatograph coupled to a mass spectrometer [41, 42]. See the experimental design of the interventions in Fig. 1 and the detailed schedule of assessments depicted in Table 2.

**Table 2 Tab2:**
[figure not shown]
Schematic schedule of enrolment

#### Anthropometric data

Anthropometric (body weight, height, waist-to-height ratio, waist and neck circumferences, and four skin folds) and body composition (electric bioimpedance) data will be assessed at baseline and post-intervention, following respective standardized guidelines and cut-offs [38, 43–46].

#### Food intake

Food intake data will be obtained before and after supplementation using two R24h and three dietary records using the photographic record. Two R24h will be performed on non-consecutive days during the week and one at the weekend. The two R24h will be held on non-consecutive days, one in the third meeting and another after 2 days by phone call. The intake of each food item will be transformed into daily consumption (grams or milliliters). After, total caloric intake, nutrients (carbohydrates, proteins, fats, vitamins, and minerals) and other specific components (fibers, carotenoids, sugars, and fatty acids) will be calculated according to the nutritional composition of each source food provided priority by the Brazilian Food Composition List (TACO) [47] and by the Household Budget Survey data (IBGE, 2010) [48] when food is not found in the first one, with the help of Microsoft Excel (v. 2016) and SPSS (v. 22) software to organize and analyze the data. The values of energy consumption, nutrients, food groups according to nutritional similarity, and food groups according to the degree of industrial processing derived from the four 24hRs will be disattenuated (corrected by intra-individual variability), generating unique values for each item. This will be achieved through the PC-SIDE program (Department of Statistics, Iowa State University, Iowa, USA) developed by the National Research Council and Iowa State University [49]. Moreover, consumption values will be adjusted for energy intake by the residual method [50]. The outpatients will be instructed not to change their dietary patterns.

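### The second 'before' diet recall falls after dosing starts and the four recalls appear to be pooled, so a recall-based food-intake covariate would mix pre- and post-treatment diet

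*Protocol article*

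**What the plan says.** All references are to the protocol article.

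- **Food intake** promises data from both periods: "Food intake data will be obtained before and after supplementation using two R24h and three dietary records". It places the two recalls as follows: "The two R24h will be held on non-consecutive days, one in the third meeting and another after 2 days by phone call".
- **Procedures** fixes the third meeting as the start of treatment: "in the third meeting, the acute supplementation phase will begin". The first recall is taken during the three-hour wait after the capsules. The 28-day supply is handed out at the end of that visit. Then: "Two days after this last meeting, the patients will report by phone call their R24h". All assessments are repeated at the last meeting.
- **Procedures** also has participants told at the second meeting, before dosing, to complete three dietary records. It later says that these records are administered during the three-hour wait.
- **Food intake** describes the processing of the recalls: values "derived from the four 24hRs will be disattenuated (corrected by intra-individual variability), generating unique values for each item". It makes no split by period at this step, and it mentions only the recalls, not the dietary records.
- **Data treatment and statistical aspects** sets time as the repeated factor and treatment as the between-group factor, with "the other variables (e.g., anthropometric data, food intake, blood analysis) as covariates". It does not say which diet instrument or period supplies the covariate.

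**The concern.** A covariate in a randomised comparison should carry information that treatment cannot have influenced. Here one of the two recalls labelled 'before' describes a day on capsules, and the pooling step seems to add the two end-of-study recalls as well. If that value enters the ANOVA, the arms are compared conditional on something measured partly after treatment began. This can distort the treatment contrast if the capsules alter eating or its reporting differently by arm. The protocol itself expects eructation with an unpleasant gastric odour, which is one conceivable route.

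There is a second loss. Participants are told not to change their diet, and a single value across both periods cannot show whether they complied. Restricting the model to 'baseline' covariates would not fully cure the problem if baseline means the 'before' recall round, because half of that round is post-dose.

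**Working it through.** **1. Reproduce the stated count.** Two recalls per round × two rounds (before, after) = 4, which matches the four recalls in the pooling sentence. Another sentence in the same section describes two weekday recalls plus one at the weekend. That gives 3 per round, or 3 × 2 = 6, which does not match. The figure of four therefore fits two per round with both rounds taken together.

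**2. Sort the diet data by the first dose.** I sort by the day the recall describes, not by the time of interview.

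| Diet data | When | Intake described |
|---|---|---|
| Recall 1 | Third meeting, after a 12-h fast, during the wait after the capsules | Essentially pre-dose |
| Recall 2 | Phone, two days later | Post-dose |
| Recalls 3 and 4 | After-supplementation round | Post-dose, by design |
| Three dietary records, first set | Instructed at the second meeting | Pre-dose, if completed before the third meeting |

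**3. Shares.**
- Recalls in the 'before' round that are post-dose: 1/2 = 50%.
- Recalls in the pooled value that are post-dose: 3/4 = 75%. Two of these three are meant to be post-treatment, so only the phone call is misplaced.
- All planned 'before' diet days, counting the records: 1 of (2 + 3) = 20% post-dose.

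**4. What this does to a covariate.** Suppose the pooled value behaves roughly like a simple average, and the arms differ by δ in reported post-dose intake. The covariate then differs between arms by 0.75 × δ because of treatment alone. With a slope β of outcome on the covariate, the adjusted treatment difference moves by about 0.75 × β × δ. The article gives neither β nor δ, so no bias figure can be computed. A single value per person affects the treatment main effect. It affects the treatment-by-time contrast only if the covariate is allowed to interact with time.

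**5. The per-period reading.** If the software instead yields one value per item for each round, the 'before' value still contains the day +2 recall (1 of 2). Dropping that recall leaves one pre-dose recall per person, and within-person variance cannot be estimated from a single recall each.

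**6. Precision of two recalls against four.** The reliability of a mean of k recalls is 1/(1 + r/k), where r is the ratio of within- to between-person variance. The article does not give r, so the range below is an assumption.

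| r | k = 1 | k = 2 | k = 4 |
|---|---|---|---|
| 1 | 0.50 | 0.67 | 0.80 |
| 2 | 0.33 | 0.50 | 0.67 |
| 4 | 0.20 | 0.33 | 0.50 |

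**The case against.** The strongest reply is that baseline diet information exists. The third-meeting recall follows a 12-h fast and describes intake before the capsules, and three dietary records are instructed before the dosing meeting. A reader might infer from the schedule that the trial has no clean baseline diet at all. The documents do not support that: up to 1 + 3 = 4 pre-dose diet days are planned. The records taken before and after could also check for dietary change even if the recalls are merged. This stands, with one caveat. The Procedures section mentions the records both at the second meeting and during the post-capsule wait, so when they are completed is unclear.

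Second, pooling across periods is a reading, not an explicit statement. The phrase about unique values could mean one value per item per round, and the section opens by promising data from both periods. The statistical section does not say that the pooled recall value is the covariate, and exact covariate definitions are often left to an analysis plan. This also stands as a limit on certainty. It does not rescue the schedule, because the misplaced phone call contaminates the 'before' value on either reading.

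Third, the practical effect may be small. Participants are blinded, they are asked to keep their diet unchanged, the day +2 recall follows very little exposure, and diet is not an outcome. I accept this. The larger issue is the two end-of-study recalls, if they enter the covariate.

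Finally, the sentence that implies three recalls may be a slip for the three dietary records. That is plausible, and it makes the correction editorial, but the counts still need to agree.

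**Conclusion.** The point holds as a contaminated covariate. It is firm that the second 'before' recall comes two days after dosing starts, since the Food intake and Procedures sections agree on this. It is the most natural reading, though not an explicit statement, that all four recalls become one value per item. On that reading 75% of the recalls behind the value are post-dose, and it can serve neither as a baseline nor as a measure of change. On the per-period reading, 50% of the recalls behind the 'before' value are still post-dose.

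The article does not show that the treatment comparison is materially biased. That would need an arm difference in post-dose diet or its reporting, an association of diet with the outcome, and use of the recall value as the covariate. None of these can be quantified from the text. I expect the effect to be modest. The reason to act is that the weakness is avoidable at very little cost.

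**What to change.** 1. Make the phone recall between the second and third meetings, before the first capsule. With allocation blinded, both 'before' recalls would then describe diet that treatment cannot have affected.
2. Run the disattenuation separately for the pre and the post round, giving two values per item.
3. Name the covariate: pre-dose intake only, from the recalls, the dietary records or both. State that the first set of records is completed before the third meeting.
4. Report the pre-to-post change in intake by arm, as a check on the instruction to keep diet unchanged. Do not use it as an adjustment variable.
5. Reconcile the recall counts in the Food intake section (two; two plus one at the weekend; four).

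**Cost.** One call moved earlier and one extra software run. The within-person correction becomes less precise with two recalls than with four: under the assumed variance ratios, reliability falls from 0.80 to 0.67 at r = 1 and from 0.50 to 0.33 at r = 4. The three pre-dose records could recover this. If each record is as informative as a recall, five days give 1/(1 + 1/5) = 0.83 at r = 1 and 1/(1 + 4/5) = 0.56 at r = 4.
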